# Primary and secondary outcomes of the study

Primary outcome measures

1. Feasibility and acceptability of the intervention (Time frame: 6 weeks post-randomisation and baseline assessment).
2. Measures to include: applicability, dosage and duration of the intervention, compliance, attrition, and adverse health effects such as appetite suppression, dietary changes and muscle soreness (Time frame: 6 weeks post-intervention).

Secondary outcome measures for exploratory analyses

1. Difference in physical performance measures: Short Physical Performance Battery^26^ (balance, 4m-gait speed, 5-chair stands) (Time frame: at baseline and after 6 weeks of intervention).
2. Difference in muscle strength measure: maximum strength test^27^ (grip strength, GS; Jamar hand-held 5030J1 dynamometer) (Time frame: at baseline and after 6 weeks of intervention).
3. Difference in muscle mass measure: Bioelectric Impedance Analysis (BIA; Tanita MC-780MA Body Composition Analyzer) (Time frame: at baseline and after 6 weeks of intervention)^28^.
4. Difference in self-reported quality of life measure: SF-12 (Time frame: at baseline and after 6 weeks of intervention)^29^.
5. Difference in activities of daily living measure: Barthel Index^30^.

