7. Muscle strength: maximum grip strength measured 3 times in each arm
8. Physical performance: Short Physical Performance Battery^26^ (balance, 4m-gait speed, 5-chair stands)
9. Muscle mass (body composition), as measured by Bioelectric Impedance Analysis (BIA; Tanita MC-780MA Body Composition Analyzer).

Baseline assessments of blood pressure and muscle mass (body composition) will be conducted at the intervention site (The Parks, Contours gym) before the first RE session, and dietary intake and appetite will be assessed during the post-exercise recovery period. Body analyser will be parts tested by the NTGH.

Detailed health and functioning profile will involve minimal risk and inconvenience to participants and will be conducted under 70 minutes (including verification of the informed consent and excluding assessments done at The Parks).

- INTERVENTION: MILK/ CONTROL DRINK + RESISTANCE EXERCISE (main team member(s) responsible: certified exercised physiologist and [name])

Thirty participants will be randomized into three groups (10 each; 5 men and 5 women):

1. ‘whole milk + RE’;
2. ‘skimmed milk + RE’, and
3. ‘control drink’ (juice supplemented with carbohydrates) + RE’.

Resistance exercise programme

RE will be conducted over 6 weeks (twice a week on two non-consecutive days) at The Parks, Contours gym & fitness suite, North Shields, North Tyneside Council in a small group of 2-3 participants, and will be supervised by a trained and experienced exercise physiologist. Participants will be advised to resume their usual diet, and to have their regular breakfast before the intervention. Four sets of 8-12 repetitions (upper and lower body) exercises at the sub-maximal level of effort (70-79% 1-repetition maximum) will be performed after a short warm-up exercise (e.g. 5 minutes of stretching exercises, walking or stationary cycling)^36,37^. Each set of RE will be followed by 1-2 minute of resting period, and a rest of 4 seconds between repetitions^36^. Each participant will receive a booklet with diagrams and short instructions of exercise programme (RE booklet). To increase their engagement in exercise, each participant will have the opportunity to record in the RE booklet how many repetitions and how much weight for each set of exercise they have completed and lifted.

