Milk / control drink will be consumed as a bolus intake of 500ml under the supervision of a researcher immediately after exercise over 40-50 minutes during the recovery period (or longer if needed). Participants will be advised to resume their usual diet. Second dose of 500ml will be consumed at participants’ home over the next 4-5 hours. All drinks consumed at home will be clearly labelled as either ‘MIlkMAN study milk’ or ‘MIlkMAN study juice’. Second dose of 500ml can be consumed with other foods as a part of their usual diet (e.g. tea, cereal, mushed potatoes, etc.). Participants will be contacted by phone in the evening to check for muscle soreness and compliance with milk/ control drink consumption. Each participant will be provided with a plastic measuring jug (500ml) and a log sheet to measure and record milk/control drink consumption at home and to report it back to a researcher conducting the phone call.

On average, 500ml milk contains ~20g of protein needed to stimulate muscle protein synthesis above stimulation provided by RE. Whole (cow) milk (nutritional estimates of 22 UK samples during winter and summer) provides 66 kcal/100g of energy^44^. Fresh milk will be provided by Arla® (Nutrition Specialist: [name] at Arla Foods). Arla Cravendale® whole milk contains 3.6g fat, 3.4g protein, and 4.7g of carbohydrates per 100g of milk. Arla Cravendale® skimmed milk contains 0.3g fat, 3.6g protein, and 4.9g of carbohydrate per 100g of milk. Energy of control drink (cranberry juice; Ocean Spray Classic) will be balanced to match whole milk energy content and supplemented with maltodextrin (e.g. cranberry juice (45kcal/100g of energy^44^) will be supplemented with 6.05g of maltodextrin (3.8kcal/g) per 100g of juice; 1tsp = 15kcal; 30.25g for 500ml of juice).

Milk and control drink storage and handling

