Milk (whole and skimmed) will be provided by Arla® (contact person: [name], Senior Nutrition Specialist, Arla Foods, Aarhus, Denmark; [contact]) in packs of either 500ml or 1 litre on a bi-weekly basis through a local distributor (Tesco or Sainsbury’s), and refrigerated at the Campus for Ageing and Vitality, Newcastle University for a long-term storage (parts tested fridge with a lock). Arla Cravendale® milk stays fresh for 21 days if left unopened. Control drink (cranberry juice) will be bought fresh weekly (Tesco) and refrigerated in a similar fashion. Control drink will be supplemented with maltodextrin at the day of intervention by a research team member. During the intervention period of the study, a researcher not involved in exercise intervention will transport milk/ control drink in cooler boxes to The Parks on daily basis. At The Parks, a fridge (parts tested) will be provided in a designated recovery room for a short-term storage of milk/ control drink.

The total time needed to complete the first visit at The Parks is about 2 and half hours (gym induction programme, assessments, intervention and recovery). This first visit will include blood pressure, body composition, diet and appetite assessment as a part of baseline assessment. The total time needed to complete the remaining RE + drink intake sessions (including recovery period) is 1 hour and 45 minutes. For participants who need more rest, additional times will be provided. The last (12th) visit at The Parks will include body composition, blood pressure, diet and appetite assessment after exercise as a part of post-intervention assessment and will last 2 hours and 10 minutes.

Individual transport will be provided to transport participants to The Parks and back home.

Those who prefer to use public or personal transport or to walk will be reimbursed for their fare.

- HOME-BASED POST-INTERVENTION ASSESSMENT (main team member(s) responsible: [name])

A post-intervention visit, in the participants own home, will be arranged after 6 weeks of intervention to assess the following domains:

1. Physical performance: Short Physical Performance Battery (balance, 4m-gait speed, 5-chair stands)
2. Muscle strength: maximum strength test (grip strength, GS; Jamar hand-held 5030J1 dynamometer)
3. Muscle mass: Bioelectric Impedance Analysis (BIA; Tanita MC-780MA Body Composition Analyzer)

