4. Dietary intake: 24-hr dietary recall (Intake24 (https://intake24.co.uk/) multi-pass, computerised 24-hr recall supported by the Newcastle University)
5. Appetite assessment: a 4-item Simplified Nutritional Appetite Questionnaire
6. General health and functioning: Self-reported quality of life: SF-12; Activities of daily living: Barthel Index; blood pressure (systolic and diastolic)

Participants’ feedback will be collected at the end of follow-up assessment using a combination of structured multiple-response and standardised open-ended questions to explore the following themes:

1. Attitudes and barriers of 2 × 500ml milk intake post-exercise (e.g. volume of liquid, taste, etc.)
2. Their opinion about milk as a functional food for muscle strength/ function
3. Appetite changes, changes in habitual diet because of milk/ control drink intake
4. What they liked and disliked about the study (intervention).

The follow-up visit will be completed within 50 minutes.

Muscle mass (body composition), appetite assessment (a 4-item Simplified Nutritional Appetite Questionnaire), dietary intake (24-hr dietary recall) and blood pressure will be assessed at the last (12^th^) intervention visit during the 45 minutes recovery period at The Parks.

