# Data analysis and statistical methods

The primary objectives of this pilot study are to assess the feasibility and acceptability of milk in combination with exercise as an intervention to improve muscle health in older adults aged ≥65 who may be at risk of developing sarcopenia in order to inform a main grant application. As such the sample size of this pilot study is limited to 30 participants and we do not make any claims of statistical power, especially for quantitative data. However, the data gathered will be explored for differences between the intervention and control group for the following quantitative measures after 6 weeks of intervention: physical performance, muscle strength, muscle mass, self-reported quality of life, and activities of daily living. We will evaluate the use of SARC-F tool for pre-screening of participants for whom is safe to be included in community-based intervention studies involving exercise. We will correlate data collected with SARC-F with the measures of muscle strength and function assessed at screen assessment. We will use descriptive and univariate/ multivariate statistical techniques in SPSS and Stata. Compliance with milk and control drink will be calculated as a percentage of actual consumption divided by expected consumption over the 6-week intervention. Calculations of the number of repetitions for each exercise within each RE session and the weight lifted will allow for calculation of several indices of training intensity. Participants’ experiences and views about the study will be also assessed with standardised open-ended questions. Data gathered form these questions will be analysed using qualitative analysis techniques, namely: content analysis. Content analysis involves the interpretation of the context of data whereby data is read and openly coded to break it down into emerging themes and sub-themes. A summary of the themes and sub-themes is then defined with the relevant quotations of the participant’s perspective. The research team includes extensive experience in both quantitative and qualitative data analysis.

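### Body composition by bioimpedance is read before exercise at baseline but after exercise, in the drink window, at visit 12, so within-arm change carries an acute shift

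*Protocol*

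**What the plan says.** Four places in the Protocol's Data collection section bear on this.

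- **Baseline** (home-based baseline assessment). Readings of "blood pressure and muscle mass (body composition) will be conducted at the intervention site (The Parks, Contours gym) before the first RE session". The same sentence puts diet and appetite into the recovery period after exercise.
- **End, first statement** (milk and control drink storage and handling). "The last (12th) visit at The Parks will include body composition, blood pressure, diet and appetite assessment after exercise".
- **End, second statement** (closing paragraph of the home-based post-intervention assessment). Muscle mass, appetite, diet and blood pressure are assessed at the 12th "intervention visit during the 45 minutes recovery period at The Parks". The numbered list earlier in that subsection still names BIA and blood pressure among the home-visit items.
- **Drink** (milk and control drink intake). The first 500 ml is "consumed as a bolus intake of 500ml under the supervision of a researcher immediately after exercise over 40-50 minutes". The order of drink and BIA is not given.

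The section on primary and secondary outcomes lists "Difference in muscle mass measure: Bioelectric Impedance Analysis" at baseline and after 6 weeks, under exploratory analyses. Data analysis and statistical methods says that "the data gathered will be explored for differences between the intervention and control group". The section on ethical considerations uses the same analyser, before and after the intervention, to watch for gains in weight and fat. The resistance exercise programme subsection has blood pressure taken both before and after every session.

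**The concern.** A change score is interpretable only if both readings are taken in the same state. Here the first is taken before exercise and before that visit's study drink. The second follows a session of up to an hour and falls in the period when half a litre is being drunk. That BIA output responds to body water and weight is general measurement knowledge rather than something the protocol states, but it is why the difference in state matters.

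Three uses of the data have no comparison group to absorb the shift: the change within each arm, the weight and fat check, and the individual before-and-after reports listed under Dissemination, so far as those include body composition. The means and standard deviations of BIA change would also be passed on to the planned larger study, and supplying data for that study is one of the pilot's aims.

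**Working it through.** The protocol gives no effect size, standard deviation or power for muscle mass, so there is no stated figure to reproduce. The check compares the timings and then works out where the shift goes.

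**1. Timings side by side**

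| Measure | Baseline (visit 1) | End (visit 12) | Same state? |
|---|---|---|---|
| BIA | before exercise | after exercise, in recovery | no |
| Blood pressure (as assessment) | before exercise | after exercise, in recovery | no, but a pre-exercise reading also exists |
| Diet, appetite | after exercise | after exercise | yes |

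Only BIA and blood pressure change state. The two statements about visit 12 agree with each other, so this is not a single slip of wording.

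**2. Visit lengths.** Exercise of 60 min plus 45 min recovery gives 105 min, which is the stated 1 h 45 min for an ordinary visit. The last visit is stated as 2 h 10 min, or 130 min, and 130 − 105 = 25 min extra. That agrees with assessments added after exercise. It does not settle whether BIA comes before, during or after the drink.

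**3. Where the shift goes.** Let T be the true 6-week change in an arm and a the acute shift at visit 12, with a = e + f (e from exercise, f from the drink). The baseline reading precedes both, so it carries neither.

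- Within an arm: observed change = T + a.
- Between arms: observed difference = (T_milk − T_control) + (a_milk − a_control).

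If a is equal in all arms, the second bracket is zero. The full a remains in every within-arm change.

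**4. Size of the drink part.** Assume a density of 1.00 to 1.05 kg per litre (not in the documents).

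- BIA before the drink: f = 0 kg of body mass.
- BIA after the full drink: f = 0.5 × 1.00 = 0.50 kg to 0.5 × 1.05 = 0.525 kg.

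So f runs from 0 to about 0.5 kg of body mass. The fraction read as lean mass is not given. The exercise part e is present whatever the drink order. The documents give neither its size nor its sign, and fluid lost in exercise would act against f.

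**5. What it would take to bias the comparison between arms.** Suppose, as an illustration only, that one arm had on average drunk a share s more of its 500 ml by the time of BIA. The body-mass difference is about 0.5 × s kg. For s = 20% this is 0.10 kg, and for s = 50% it is 0.25 kg. For s = 0 and equal acute responses it is 0.

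**6. After the change.** With both readings taken before exercise and drink, e = f = 0 at visit 12 and the observed change estimates T. No sample size or power figure moves.

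**The case against.** The strongest reply is that the planned comparison is between arms. All three arms share the exercise programme, the visit schedule and the 500 ml volume, so a common shift cancels. This stands. A reader might infer that the comparison of milk with control is biased, but the documents do not show that. Bias there needs an acute response, or an amount drunk before BIA, that differs by arm. The drinks do differ in composition and the order is not fixed, so a difference is possible, but nothing in the protocol shows one or gives its size. Uneven timing between participants could add noise, again of unknown size.

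Second, blood pressure is largely covered. It is not a listed outcome, and a pre-exercise reading is already planned at every session, including the twelfth. A reader might take it to be as compromised as BIA. It is not: only the choice of which reading counts as the post-intervention value needs correcting.

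Third, size. A reader might set 0.5 kg against an assumed lean-mass gain of 0.3 to 1.0 kg and conclude that the artefact is 50% (0.5/1.0) to 167% (0.5/0.3) of the effect. The documents do not support that ratio. The gain is not in the protocol, 0.5 kg is scale weight rather than lean mass, and it is reached only if the whole drink precedes BIA. With BIA first, the drink part is zero. If the net shift differs in sign between people, some of it appears as noise rather than as average bias.

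Fourth, this is an exploratory outcome in a 30-person feasibility pilot that disclaims power. That limits the severity. It does not remove the mismatch, which lies in the data-collection instructions and cannot be repaired in an analysis plan.

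**Conclusion.** The point holds for BIA. The protocol measures body composition in two different states, and the difference enters the within-arm change in muscle mass, the weight and fat check, and any individual report that uses these values. The drink contributes between 0 and about 0.5 kg of body mass, depending on an order the protocol does not fix. The exercise contribution is additional and unquantified, and may partly offset it. These statements rest on an assumed drink density near 1 kg per litre and on BIA responding to recent exercise and fluid.

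The comparison between arms is protected to the extent that the shift is common to all arms. Blood pressure needs a change of label, not a new measurement. The primary conclusions on feasibility and acceptability do not depend on any of this. It is a cheap and worthwhile correction, not a threat to the trial's main purpose.

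**What to change.** - At visit 12, take BIA before the resistance exercise session and before any study drink, as at visit 1.
- Name the pre-exercise blood pressure already planned at that session as the post-intervention value, and keep the post-exercise reading as session monitoring.
- Reconcile the three timing statements: the baseline sentence, the description of visit 12 under milk and control drink storage and handling, and the closing paragraph of the home-based post-intervention assessment. Remove BIA and blood pressure from the numbered home-visit list, or mark there that they are done at the gym.
- If any participant has already been measured after exercise, record the time of BIA and the volume drunk by then. Report those within-arm changes with that caveat.

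The cost is protocol wording and a changed order within one visit. The device, the staff and the number of visits stay the same. Diet and appetite can remain in the recovery period, since they are assessed after exercise at both time points.

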Except for intervention (6 consecutive weeks), this time scale can be adjusted to participants’ individual needs with maximum 2-3 weeks gap between baseline assessment and the first week of intervention, and maximum 2-3 weeks gap between the last week of intervention and post-intervention assessment.

[figure not shown]

*Figure 2*. Flow diagram of participants’ journey through the study.

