There is also a small risk of gastrointestinal discomfort and possible unknown milk allergies (lactose or milk proteins). Participants who report any significant discomfort associated with milk or control drink intake (e.g. nausea, indigestion, diarrhoea, etc.) will be excluded from the study. In addition, there is a small risk of metabolic changes and weight gain due to the consumption of 650 kcal from whole milk and control drink (2 × week over 6 weeks) which will be counteracted by the increased energy expenditure during the RE programme. Appetite will be assessed at baseline and post-intervention, and total energy intake will be estimated using the Intake24 (computerised 24-hr dietary recall) pre- and post-intervention to examine any changes in energy intake. Also, weight and body fatness will be estimated using the Tanita Body Composition Analyzer at baseline and after the intervention.

There is also a small risk of falling during the walking test. However, the attending researcher will assess individual risk at the point of data collection (re-check exclusion criteria and endurance of consent) and omit measurements/ test if they felt it unsafe or that capacity to consent is not present or consent does not endure. It is made clear to participants that they are free to withdraw at any time. Should a decision to withdraw from the study be made, a reason for the withdrawal will be recorded. However, participants can withdraw without providing any explanation.

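### The single-day diet recalls are tied to sessions 1 and 12 with no weekday matching, so the before-after change in energy intake may be confounded with day of week

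*Protocol*

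**What the plan says.** Under Data collection, the protocol places the baseline recall at the first gym visit: "This first visit will include blood pressure, body composition, diet and appetite assessment as a part of baseline assessment". It is taken after training: "dietary intake and appetite will be assessed during the post-exercise recovery period". The final recall is at session 12: "The last (12th) visit at The Parks will include body composition, blood pressure, diet and appetite assessment after exercise". Diet also appears in the list of domains for the home-based post-intervention visit, but the end of that section settles the timing: "dietary intake (24-hr dietary recall) and blood pressure will be assessed at the last" intervention visit. One recall per time point is described, with no repeat days.

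The schedule is given as "RE will be conducted over 6 weeks (twice a week on two non-consecutive days"), and the Flow diagram section holds the training weeks fixed: "Except for intervention (6 consecutive weeks").

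The section on ethical considerations, risk and burden states how the recalls are used: "total energy intake will be estimated using the Intake24 (computerised 24-hr dietary recall) pre- and post-intervention to examine any changes in energy intake". Dietary change is listed among the adverse effects in the primary outcome measures, and the second hypothesis expects no negative dietary changes.

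The protocol does not say that a participant keeps the same two weekdays, which weekdays the gym sessions use, which day starts the programme, which 24 hours the recall covers, or that recall weekdays are matched or recorded.

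**The concern.** A single-day recall measures intake on one particular day, so a before-after difference contains whatever separates those two days as well as any effect of the programme. Tying the recalls to the first and last of an even number of sessions means that, under a regular timetable, they do not fall on the same weekday. If intake differs between weekdays and the order of days is similar across participants, part of the observed change is a weekday effect. A fall from a Sunday to a weekday could then be taken for a dietary change during the intervention, or could offset a real rise. The reading most exposed is the one the protocol proposes: the pre-to-post change in energy intake within participants, without reference to the control arm.

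**Working it through.** **Session count.** 2 sessions per week × 6 weeks = 12, which agrees with the protocol's twelfth and last visit.

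**Weekdays under fixed days (assumption).** With days A and B and a start on A, sessions 1, 3, …, 11 fall on A and sessions 2, 4, …, 12 on B. Session 1 is odd and session 12 is even, so they differ.
- Monday-Friday: 6 non-consecutive pairs × 2 possible starting days = 12 cases; same weekday in 0.
- All seven days: 21 pairs − 7 adjacent pairs = 14; 14 × 2 = 28 cases; same weekday in 0.
- Sessions 1 and 11 are 5 × 7 = 35 days apart, so they share a weekday in every case.

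**Recalled days, if the recall covers the previous day (assumption).** Start on the earlier day of a Monday-Friday pair:

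| Session days | Baseline recall | Final recall |
|---|---|---|
| Mon, Wed | Sun | Tue |
| Mon, Thu | Sun | Wed |
| Mon, Fri | Sun | Thu |
| Tue, Thu | Mon | Wed |
| Tue, Fri | Mon | Thu |
| Wed, Fri | Tue | Thu |

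A Sunday appears at baseline in 3 of 6 pairs and at the end in 0 of 6.

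**Direction.** With equally likely Monday-Friday pairs, the mean change in the share of weekend days recalled is:
- all start on the earlier day: −3/6 = −0.5;
- all start on the later day: +3/6 = +0.5;
- starts evenly mixed: 0.

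If weekend sessions are allowed and all 14 pairs are equally likely, the shift is −1 in 4 pairs, 0 in 6 and +1 in 4, so the mean is 0.

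**If days are not fixed.** Suppose a Monday-Friday pair is redrawn at random each week, in whole calendar weeks. Session 1 is the earlier session of week 1 and falls on Wednesday with probability 1/6. Session 12 is the later session of week 6 and falls on Wednesday with probability 1/6. Wednesday is the only day both can share, so they match with probability 1/6 × 1/6 = 1/36.

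**Size, for illustration only.** The protocol gives no weekend-weekday difference and no SD. Let d be the weekend excess in intake, assumed to be 0 to 300 kcal, and let s be the share of participants who go from a Sunday to a weekday, with the rest having weekday-only pairs. Bias = −s × d.
- s = 1: 0 to −300 kcal.
- s = 0.5: 0 to −150 kcal.
- Evenly mixed starts: about 0.

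For scale, the standard error of a mean change is √2 × SD / √n. With an assumed within-person SD of 400 to 600 kcal this is 103 to 155 kcal for n = 30 and 179 to 268 kcal for n = 10.

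**The case against.** The bias is conditional. The protocol requires two non-consecutive days a week. It does not say that the days are fixed, that sessions run Monday to Friday, or that everyone starts on the earlier day. Different weekdays within a person do not by themselves shift a group mean; that also needs a common order of days and different intake on those days. This stands, and it limits the claim. Varying the days does not restore matching, however, and the example timetable (training from week 2 or 3 to week 7 or 8) suits whole weeks better than mid-pair starts.

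The trial has a concurrent control arm, and nothing links weekday to arm, so any shift cancels in expectation between arms. This stands too. Weekday is not a minimisation factor (gender and grip strength are), so chance imbalance is possible with 10 per arm.

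Dietary change is one example within a broad feasibility outcome. The data analysis section does not list it among the quantitative measures to be compared, and it claims no power. Appetite has its own questionnaire, participants are asked directly about changes in habitual diet, and weight and body fatness are measured. A misleading recall difference would therefore not stand alone.

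A reader might also infer that the mismatch hides the energy added by the study drink. The document does not support this. Drinks are taken on session days, the second within 4-5 hours, and sessions are never on consecutive days, so a previous-day recall at session 12 does not cover a drink day. If the recall instead covers the 24 hours up to the visit, each recall mixes two calendar days and the Sunday-to-weekday contrast itself weakens.

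**Conclusion.** The point holds as a limited design weakness. Taking the recalls at visits 1 and 12 as written leaves weekday unmatched: always under fixed session days, and in 35 of 36 cases on average under randomly varying Monday-Friday days in whole weeks. The uncontrolled before-after change in energy intake may therefore be confounded with day of week. A directional bias further requires Monday-Friday sessions, a common start on the earlier day, previous-day recall, and intake that differs between Sunday and weekdays. None of these is stated.

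A reader might infer that the design builds in a systematic bias of known direction and size. That goes too far: the direction reverses or vanishes with the starting day, and every kcal figure rests on assumed inputs. With mixed starts the consequence is extra noise in an already noisy single-day measure. The between-arm comparison is unbiased in expectation. This is a low-priority improvement and does not threaten the pilot's main feasibility conclusions.

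**What to change.** State that the final recall must cover the same weekday as that participant's baseline recall, and take it at whichever week-6 visit achieves this. When session days are fixed, that is session 11. Record the recalled weekday on the CRF at both time points, so that any mismatch from a moved or missed session can be seen and reported.

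No visit or measurement is added. Visit 11 (planned at 1 hour 45 minutes) becomes longer and visit 12 (planned at 2 hours 10 minutes) shorter. The recall is separated by a few days from the other measures taken at visit 12. With fixed Monday-Friday days, session 12 comes 37 to 40 days after session 1 and session 11 comes 35 days after, so the gap is 2 to 5 days.
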